##### Primary outcomes

Objectively measured physical activity. Objective measures of PA are obtained through Actigraph GT9X accelerometers. The accelerometer is worn on the wrist and participants are instructed to wear the devices continuously for 7 days (day and night) during their daily activities and sleep. The sampling unit (epochs) is set to 1 s to facilitate data analysis and ensure sufficient sensitivity for low intensity activities. The participants accelerometer counts are categorized into activity levels (sedentary, light, moderate and vigorous) according to the cut-off points established by Montoye et al. [62].

Self-reported physical activity. The Short-Form of the International Physical Activity Questionnaire (IPAQ) is used to assess self-reported PA and sedentary behavior. The 9-item IPAQ measures the weekly frequency and duration of PA across three specific intensities (i.e., light, moderate, and vigorous), and time spent sitting during week and weekend days. Scores for total PA and discriminated by intensity, and for total sitting time, will be derived from the data collected (min/week) [63]. The Activity Choice Index (ACI) is employed to assess physically active lifestyle behaviors. The frequency of self-reported activities, which represent active choices made in daily routines, over the last month, are assessed using a 6-item (e.g., “using stairs instead of escalators or lifts”; “walking instead of driving or taking public transport”; “choosing to do things by hand instead of using mechanical/automatic tools”). The items are scored according to a 5-point scale, from one ("Never") to five ("Always") [64].

Quality of life. The European Organization for Research and Treatment of Cancer Quality of Life Questionnaire Core 30 (EORTC QLQ-C30) and its breast cancer module (EORTC QLQ-BR23) are used to measure changes in participants’ quality of life throughout the intervention and follow-up phases, and have previously demonstrated adequate reliability [65, 66]. EORTC QLQ-C30 comprises 30 items, organized in 8 multi-item functional (physical, role, emotional, cognitive, and social) and symptom (fatigue, pain, and nausea) subscales, one global health status and quality of life (QOL) subscale, and 6 single items (dyspnea, insomnia, appetite loss, constipation, diarrhea, and financial difficulties). Breast cancer-related symptoms and side effects are assessed with EORTC QLQ-BR23 module, comprising 23 items, organized in 5 subscales (i.e., body image, sexual functioning, systemic therapy side effects, breast symptoms, and arm symptoms). Five items specifically related to joint, bone, and muscle pain/discomfort, derived from the new EORTC QLQ-BR45 [67], were added provided the specificity of aromatase inhibitors’ side effects.

Healthcare use. Data is collected on healthcare resources use during the study period, namely number and type of consultations, drugs, medical tests and exams, in-patient stays, and day care sessions. Absenteeism is assessed using participants’ reports of their number of absence days or percentage of normal working hours worked, valued at patients’ hourly wage. These resources will then be valued using usual official sources.

##### Secondary outcomes: Physical measures

Body composition. Bioelectrical Impedance (Impedimed, Australia) is used under standardized conditions, by experienced technicians and overseen by the research team. Body weight is measured with a digital scale (SECA, Germany). Height is measured with a balance-mounted stadiometer. Body mass index in kilograms per square meter is calculated from weight (kg) and height (m). Waist circumference is measured according to the NIH protocol [68].

Upper limb perimeters. Right and left limb perimeters are measured in five anatomical points along the arms – hand knuckles with closed fingers, wrist, forearm (10 cm below the elbow line), elbow and arm (10 cm above the elbow line). Lymphedema risk is assessed through the difference between the right and left limb (hand, forearm, and arm) perimeters. A difference of 3 cm between limbs in one of the perimeters indicates risk of developing lymphedema.

Cardiorespiratory fitness. A submaximal, 8-min, single-stage walking test on a treadmill is performed to measure cardiorespiratory fitness. The test involves a 4-min warming up at a self-selected speed, at 50–70% of the individual's age-predicted maximum heart rate, and 4 additional minutes at a 5%-increased workload [69]. The steady-state heart rate at this workload and the treadmill speed, together with participants’ age and gender, are used to estimate VO2max.

Muscular strength. Handgrip and maximal strength tests are performed to assess muscular strength. Participants are instructed to hold the handgrip with their maximal strength. Maximal muscular strength is determined for chest press, horizontal seated row and leg press, using a 10-repetition maximum (10 RM) test [70]. After a standardized warm-up, gradual load increases are made until the maximum weight lifted through a full range of motion is recorded as 10 RM.

Upper limbs flexibility. Shoulder mobility protocols is used to measure flexibility. Angular measures [71] of shoulder flexion and abduction are taken on both sides using a goniometer. Linear measures are taken using the Back Scratch protocol [72] on both shoulders with a SECA measuring tape.

Physical Function. The Sit to Stand, Timed Up and Go and Stand on one-foot tests are employed to assess physical function. The Sit to Stand Test consists of standing and seating in a chair as many times as possible with arms crossed over the chest in 30 s [73]. The Time Up and Go Test is used to assess mobility by measuring the time a person takes to rise from a chair, walk 2.44 m, turn around, walk back to the chair, and sit down [74]. For the Stand on one foot test [75], participants are instructed to stand on one foot with their eyes open (both sides are tested) for a maximum of 20 s and have their time recorded.

Adverse events of anticancer treatment. A simplified version of the Common Terminology Criteria for Adverse Events (CTCAE v.5), using its broader categories (i.e., cardiac disorders, respiratory disorders, nervous system disorders, infections, skin tissue disorders, musculoskeletal and connective tissue disorders, and immune system disorders) is used at each timepoint to assess the occurrence of any adverse events in the previous 3 months.

##### Secondary outcomes: Psychosocial Measures

Perceived intervention climate. Participants’ perception of the facilitators interpersonal behaviors is measured with the Interpersonal Behaviors Questionnaire (IBQ) [76], a 24-item instrument including three support subscales—perceived autonomy, competence, and relatedness support – and three thwarting subscales – perceived autonomy, competence, and relatedness thwarting. Responses are given on a 7-point Likert scale, ranging from 1 (“do not agree at all”) to 7 (“completely agree”).

Exercise motivational regulations. The 24-item Behavioral Regulation in Exercise Questionnaire-3 (BREQ-3) [77] will be used to measure the six forms of motivation proposed by self-determination theory – amotivation, external regulation, introjected regulation, identified regulation, integrated regulation, and intrinsic motivation. Responses are given on a 5-point Likert scale, ranging from 1 (“Strongly Disagree) to 4 (“Strongly Agree”).

Exercise needs satisfaction/frustration. The 24-item Basic Psychological Need Satisfaction and Frustration Scale (BPNSFS) [78] will be used to assess satisfaction/frustration of the three basic psychological needs (autonomy, competence, and relatedness) for exercise. Responses are given on a 5-point Likert scale, from one (“Totally disagree”) to five (“Totally agree”).

Affective response to exercise. The Feeling Scale (FS) [79, 80], is an 11-point scale ranging from -5 (“Very bad”) to + 5 (“Very good”), which assesses the affective valence of exercise.

Exercise self-efficacy. The 9-item Modified Bandura’s Exercise Self-Efficacy Scale will be used to measure how certain participants are/were that they would practice exercise under different conditions or restrictions [81]. Responses are given on a 4-point Likert scale, from 1 (“Very sure”) to 4 (“Not at all sure”).

Self-regulation skills. Action planning (i.e., when, where, what to do, and how often exercise) and coping planning (i.e., how to cope with setbacks and what to do to act according to one’s intentions to exercise) will be assessed the Action Planning and the Coping Planning scales, comprising 5 items each [82]. Action control will be measured with 6 items addressing its different facets, (i.e., self-monitoring, awareness of standards, and self-regulatory effort) [83]. All items are answered on a 4-point Likert scale from 1 (“Completely disagree”) to 4 (“Totally agree”).

Subjective pain. Single items of the Brief Pain Inventory (BPI) will be used to assess pain severity “on average” and “right now”. The BPI is scored on a 10-point scale from 0 (“No pain”) to 10 (“Pain as bad as you can imagine”) [84]. The 7-item Pain Disability Index (PDI) will be used to evaluate the impact and interference of pain on participants’ daily activities and functioning (i.e., family and home responsibilities, recreation, social activity, occupation, sexual behavior, self-care, and life-support activities). Each item is rated on a 10-point scale, from 0 (“No Disability”) to 10 (“Worst Disability”) [85, 86].

Sleep quality. The 19-item Pittsburgh Sleep Quality Index [87] will be used to measure sleep duration and sleep disturbance components of sleep quality. Each item is rated on a 4-point scale, ranging from 0 (“Not during the past month”) to 3 (“Three or more times a week”).

Body image. The 10-item Body Image Scale (BIS) [88] will be used to assess participants’ affective (e.g., feeling self-conscious), behavioral (e.g., difficulty at looking at the naked body), and cognitive (e.g., satisfaction with appearance) dimensions of body image. Responses are given on a 4-point Likert scale, from 0 (“Not at all”) to 3 (“Very much”).

Depressive symptoms. The 7-item depression subscale from the Hospital Anxiety and Depression Scale (HADS) [89, 90] will be used to measure depression. Responses are given on a 4-point Likert scale, from 0 (“Never”) to 3 (“Most of the time”). HADS scores can be categorized into normal (0–7 points), mild depression (8–10 points), moderate depression (11–14 points) and severe depression (15–21 points).

Psychological well-being. Four items, asking participants to rate their overall satisfaction with life, optimism, and purpose of life and daily activities, will be used to measure the various dimensions of psychological well-being [91]. Responses are given on a 10-point scale, from 0 (“Not at all”) to 10 (“Completely”).

##### Potential covariates

Demographics such as age, education level, professional status, marital status, smoking history, alcohol consumption, medical factors (i.e., breast cancer stage, cancer treatment types, time since diagnosis, time since treatment, length of AI therapy, comorbid conditions, and current medications, blood pressure, and resting heart rate) will be considered as potential covariates. Participant’s medical history will be confirmed by personal medical reports brought by participants. Given that dietary habits and caloric intake, unrelated to our interventions, may affect body composition, participants will complete the adapted version of the Dietary Instrument for Nutrition Education (DINE) [92]. DINE measures self-reported dietary behavior by examining the frequency of intake of 19 food/drink items (e.g., cheese, burgers/sausages, beef, pork/lamb, chips, bacon/ham, savory pies/snacks, fruits, vegetables, sweets, biscuits, sugary drinks, milk). Alcohol consumption and frequency of breakfast will also be assessed.

#### Process Evaluation

A process evaluation will be embedded in the RCT to provide insight into whether the two intervention programs are being delivered as intended; identify potential barriers and facilitators of implementation; explore why they did or did not produce the intended outcomes; and assess participants’ and interventionists’ experiences of the program. At post-program and final follow-up measurements, the two intervention groups will be asked to join focus groups focusing on: experiences with the program, toolkit, and resources available; which elements they found most useful; the extent to which they are still interacting with their peers after the program has ended; and the perceived impact of the programs on their lives (barriers and facilitators of behavior change). A logbook will also serve to assess easiness of implementation and adherence to sessions. This logbook, fulfilled weekly by the session facilitators, includes session attendance, implementation of each session components (vs deviations), and additional comments/unexpected events. Interviews with session facilitators and healthcare providers involved in recruitment, exploring their experiences with the program (barriers and facilitators) will also be conducted at intervention´s end.

#### Statistical methods

Factorial Anovas with repeated measures, adjusting for potential covariates (e.g., primary treatment, length of AI therapy), will be conducted for primary and secondary outcomes. The analysis will be intent-to-treat to include compliance effects in the overall assessment. Last Observation Carried Forward will be used to impute missing values. A per-protocol analysis will also be conducted without participants who do not attend at least 80% of the sessions. Normality plots and Kolmogorov–Smirnov tests will be used to test normality of outcome variables. If substantial departure from normality is found, square root log transformations will be computed. If normality is still not satisfied, non-parametric tests (e.g., Kruskal–Wallis) will be employed. As the experimental design is factorial, multiple comparison adjustments will not be appropriate.

Mediators of change, i.e., mechanisms by which participants change their lifestyle behaviors and QoL (vs. controls), will be explored using structural equation modeling (AMOS 18.0) and multiple mediation analysis (PROCESS macro v. 3.3 for SPSS). Putative candidates will include motivational (e.g., autonomous motivations) and self‐regulatory (e.g., action planning) variables. Mediation is said to occur when the causal effect of an independent variable (X) on a dependent variable (Y) is partially or fully explained by a mediator (M) [93]. Indirect effects will be tested using Preacher and Hayes’ procedures [94]. Bootstrapping with 5000 samples and 95% CI estimates for indirect effects will be calculated and assumed significant (α = 0.05) if the CI does not encompass zero [95, 96]. The ratio of the indirect effects to the total effects (P_*M*_) will be calculated to express the strength of the mediation effects [95]. Moderators, i.e., baseline characteristics that have an interactive effect with the intervention on the outcome(s), will be assessed to better understand individual differences in intervention effects [97, 98]. Moderation effects on primary outcomes will be conducted at intervention or follow-up’s end.

A cost-effectiveness analysis will be conducted, from the NHS and societal perspectives, in comparison with the “no intervention” arm. The time horizon of the study will coincide with that of the intervention follow-up, so that no specific modeling tools will be used. Quality-adjusted life years (QALYs) will be estimated using EORTC QLQ-C30 collected during the intervention, mapped to EQ-5D using mapping algorithms from the literature [97]. Intervention costs will be estimated using a bottom-up approach [99]. Attendance to PA counseling and exercise sessions will be registered; exercise physiologists’ time-related costs will be estimated using their gross hourly salaries, and equipment and disposables’ costs through invoices. Healthcare resources will include consultations, drugs, tests and exams, in-patient stays and day care sessions, valued using usual official tariffs. Absenteeism will be assessed using participants’ reports of their number of absence days or percentage of normal working hours worked, valued at patients’ hourly wage. The incremental cost-effectiveness ratio (ICER) will be calculated as the difference in costs divided by the difference in QALYs between intervention and control groups.

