### Objectives

This paper describes the protocol of a pragmatic randomized controlled trial (RCT), PAC-WOMAN, targeting Portuguese post-menopausal women diagnosed with hormone-receptor-positive breast cancer, currently on Aromatase Inhibitors. This project primary aims are:a) To develop and test the long-term (16-month) effectiveness and cost-effectiveness of two 4-month group-based interventions, compared to a control waiting list, on promoting sustained changes in PA, sedentary behavior, QoL, and healthcare services’ use (primary outcomes)b) To compare the effects of both interventions (i.e., brief PA counseling vs. structured exercise) on long-term changes in our primary outcomes, as well as their cost-effectivenessc) Evaluate pretreatment moderators of 4-month and 16-month changes in PA, sedentary behavior, and QoLd) Identify critical motivational (theoretical) mechanisms of change in PA, sedentary behavior, and QoL, and explore their mediating role.

As secondary aims, we will study the impact of both interventions on AI therapy continuation, adverse events of treatment, disease-free survival, body composition, sleep quality, physical parameters (e.g., muscular strength), and psychosocial factors (e.g., body image). Furthermore, process evaluation will also be conducted seeking to analyze implementation facilitators and barriers.

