In sum, existing interventions targeting supervised exercise, although very effective in promoting short-term health outcomes [43], may be labor intensive and costly for staff and participants. Also, long term effects, once the intervention is finished, may be jeopardized given that supervised interventions may have the detrimental effect of patients’ internalization of the message that their condition is to be dealt with by procedures and techniques essentially under the responsibility and “steering” of an external expert (e.g., simply follow an exercise prescription), thus promoting an external locus of causality. In contrast, theory-based, evidence-informed brief counseling, delivered in a manner that reduces dependence on staff and facilitates self-regulatory skills, could alleviate time and financial barriers while promoting free-living, integrated into daily-life, PA/exercise. From a self-determination theory (SDT) perspective [28], lasting behavior change does not depend on complying with external demands for change but rather on accepting the regulation of change as one’s own. This requires internalizing the regulation of relevant behaviors and integrating them with one’s sense of self and one’s values and goals, so they can become the basis of autonomous regulation [27].

Thus, the PAC-WOMAN trial will test effectiveness and cost-effectiveness of these 2 types of interventions (supervised structured exercise vs. brief theory-based PA counseling) against a waiting-list, standard care, control group. This is of importance given that although an improved health profile (e.g., lower blood pressure, lower body mass index, improved tumoral biomarkers, cardiorespiratory fitness, physical function) is expected as a short-term result of the exercise intervention, the maintenance of the PA/exercise habits after the end of the intervention remains to be determined (and consequently its long-term health outcomes). On the other hand, will a brief motivational (SDT-based) intervention (lighter in time and resources) be enough to trigger a more physically active lifestyle? And will the potential behavioral, motivational, and self-regulatory changes endure in the long term? (With a sufficient magnitude to produce positive health outcomes?).

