#### Participants

Recruitment (ongoing) will aim for 122 Portuguese breast cancer survivors who have completed primary cancer treatment and are currently under aromatase inhibitors therapy and will subsequently be randomized to receive the brief PA counseling (PAC), the structured exercise program (StEx), or to a waiting list control group.

The inclusion criteria for entering this study are: 1) post-menopausal women, below 70 years old; 2) histologically confirmed hormone-receptor-positive breast cancer (stage I, II, III); 3) having initiated AI hormonal therapy following the primary treatment (surgery, radiotherapy, chemotherapy, etc.), at least 1 month before being enrolled; and 4) ECOG-Performance Status 0–1 (being able to perform light-to-moderate physical activities). The exclusion criteria are: 1) evidence of stage IV cancer or synchronous tumors; 2) uncontrolled hypertension, cardiac or pulmonary disease; 3) contraindications to exercise training according to the assistant doctor; 4) inability to provide informed consent; and 5) expected inability to fulfill the proposed program schedule.

Given the study design, sample size estimations were calculated for primary outcomes having one-way factorial analysis of variance with repeated measures as the reference statistical analysis. Based on previous research findings, and considering a 25% dropout, the sample size was estimated in 98 participants to detect a small to moderate effect size (α = 0.05; statistical power = 0.80) using G*Power 3.1. Consensual criteria on sample size needs for mediator/moderator analyses are not consensual and depend on the procedure and number of indicators and pathways in the models; therefore, we increased the estimated number of participants in 25%, obtaining a final estimated sample size of 122 participants.

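### The long-term aims rest on a four-visit, three-arm repeated-measures ANOVA, and neither of its between-arm terms isolates a difference at 16 months

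*Protocol article*

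**What the plan says.** In Objectives, primary aim (a) is "To develop and test the long-term (16-month) effectiveness and cost-effectiveness of two 4-month group-based interventions, compared to a control waiting list". Aim (b) compares the two programmes with each other on long-term change. These are pairwise questions, and aim (a) carries a fixed time.

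Assessments places the visits at baseline (T0) and at 4, 10 and 16 months (T1, T2, T3). Statistical methods gives one analysis of arm differences: "Factorial Anovas with repeated measures, adjusting for potential covariates (e.g., primary treatment, length of AI therapy), will be conducted for primary and secondary outcomes". The sample size paragraph in Participants relies on the same method: "sample size estimations were calculated for primary outcomes having one-way factorial analysis of variance with repeated measures as the reference statistical analysis", sized "to detect a small to moderate effect size (α = 0.05; statistical power = 0.80) using G*Power 3.1". Neither place names a deciding model term or a 16-month contrast. Statistical methods mentions a time point (end of intervention or of follow-up) only for moderation. It also specifies LOCF for missing values and no adjustment for multiple comparisons.

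The Rationale section explains why timing matters. A better health profile "is expected as a short-term result of the exercise intervention, the maintenance of the PA/exercise habits after the end of the intervention remains to be" seen.

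**The concern.** The trial is meant to tell a lasting change from a peak at the end of the programme. With baselines equal by randomization, the group-by-time test has as its null that the arms do not differ at any visit. It can reject because of month 4 alone. The group test dilutes a late effect with earlier visits and with baseline, where no effect is possible. With three arms, neither term says which arm differs.

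If the article's text is followed and no more, a significant result could come entirely from month 4, and nothing in the text prevents it from being read as an answer to aim (a).

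**Working it through.** **1. Which test was the trial sized on?** The article gives "considering a 25% dropout, the sample size was estimated in 98 participants" and then "we increased the estimated number of participants in 25%, obtaining a final estimated sample size of 122 participants". It states no numerical effect size or visit correlation. Assume f = 0.15, correlation ρ = 0.5 and sphericity, for a 3-arm by 4-visit interaction:

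- λ = f²·N·m/(1−ρ), with df = (k−1)(m−1) = 6 and (N−k)(m−1).
- N = 78: λ = 0.0225·78·4/0.5 = 14.04, df 6 and 225, power 0.801. N = 77 gives 0.795.
- 78 × 1.25 = 97.5, rounded up to 98. 98 × 1.25 = 122.5, stated as 122.

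The stated figures therefore fit a group-by-time test. The match depends on the assumed f and ρ, so it suggests the planned term and does not prove it.

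**2. Can that test separate transient from sustained effects?** Let both programmes differ from control by d. If the difference exists at month 4 only, f = d·√(0.5/12) = 0.204d, so f = 0.15 means d = 0.73 SD. If the difference is d at months 4, 10 and 16, the interaction f is the same 0.204d. Power is then identical for the two profiles: 80% at N = 78, 90% at N = 98, 96% at N = 122.

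**3. Rejection when the true 16-month difference is zero.** Take one programme with benefit (0, e, e/2, 0) SD at T0 to T3 and no effect in the other arms. Arm sizes: 122/3 ≈ 40, or 122 × 0.75/3 ≈ 30 after the planned dropout, with equal allocation assumed. Outcomes are normal with compound symmetry.

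- Group by time: λ = n·(2/3)·0.6875·e²/(1−ρ) = 0.458·n·e²/(1−ρ), where 0.6875 is the sum of squares of (0, 1, 0.5, 0) about its mean.
- Group: the arm's mean over visits is 0.375e, so λ = 4n·(2/3)·(0.375e)²/(1+3ρ) = 0.375·n·e²/(1+3ρ).
- Example, e = 0.5, n = 30, ρ = 0.5: λ = 6.88 gives 45% for group by time; λ = 1.125 gives 14% for group.

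Rejection at 0.05, group by time / group:

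| e (SD) | n=30, ρ=0.5 | n=30, ρ=0.7 | n=40, ρ=0.5 | n=40, ρ=0.7 |
|---|---|---|---|---|
| 0.3 | 17% / 8% | 27% / 7% | 22% / 9% | 36% / 8% |
| 0.5 | 45% / 14% | 70% / 12% | 59% / 17% | 84% / 15% |
| 0.8 | 90% / 30% | 99% / 25% | 97% / 39% | 100% / 32% |

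Simulation of the same settings gave 17-35%, 43-85% and 89-100% for group by time. When AR(1) correlation was also allowed, with a Greenhouse-Geisser correction, the ranges widened to 28-85% at 0.5 SD and 77-100% at 0.8 SD. With no effect at any visit, group by time rejected in about 5%.

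**4. A 16-month contrast under the same truth.** With complete data, a baseline-adjusted T3 contrast rejected in 4-6% of trials. Under LOCF, if 25% of each arm leave after month 4 (an assumption about timing), the carried values create an apparent T3 difference of 0.25e: 0.125 SD for e = 0.5 and 0.20 SD for e = 0.8. The T3 contrast then rejected in about 9-21% of trials.

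**5. Does the contrast lose power for a sustained effect?** For a sustained 0.5 SD effect in both programmes (ρ = 0.5, complete data), group by time has 53% power at N = 98 and 64% at N = 122. A baseline-adjusted T3 contrast against control has 65% and 74%.

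**The case against.** Only a journal article is available. Which model term decides, and which follow-up contrasts are run, are details that an analysis plan commonly settles, so their absence here is not in itself an error. The article also points towards specific comparisons: Objectives names the pairs and the 16-month horizon, and the remark on multiple comparison adjustment presupposes that comparisons will be made. A repeated-measures model is a reasonable way to study sustained change, and the remedy keeps that kind of model.

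This limits the point but does not remove it. The article states an analysis and sizes the trial on it, and neither between-arm term of that analysis answers aim (a).

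Three stronger readings are tempting and are not supported:

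- A reader might infer that the protocol will report a significant interaction as long-term effectiveness. It does not say so; the text only leaves that open.
- A reader might infer that a short-term effect would usually trigger rejection. At 0.3 SD it mostly would not, and the target is only to "detect a small to moderate effect size". The group term stays below 40% throughout.
- A reader might express these rates as multiples of 5% and call them type I error inflation. They are power against a real month-4 effect. The test keeps its level when there is no effect at any visit.

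Nor does the protocol predict complete relapse; it says that maintenance is unknown.

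**Conclusion.** The point holds as a mismatch between aim and stated test, and it should be fixed. Aims (a) and (b) need pairwise long-term differences, at 16 months for aim (a), while the stated ANOVA terms test profile shape or an average over visits. If a month-4 benefit is fully lost by month 16, group by time would still reject in about 17-35% (0.3 SD), 43-85% (0.5 SD) or 89-100% (0.8 SD) of trials, and the group term in about 7-39%. A significant term alone is therefore no evidence of a sustained effect.

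The figures assume equal arms of 30 to 40, normal outcomes, visit correlation 0.5-0.7 with compound symmetry, and the relapse pattern shown. The protocol states none of the effect sizes or correlations. The figures do not cover the non-parametric fallback, or healthcare use, which Table 2 shows as assessed once.

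**What to change.** In Statistical methods, for the primary outcomes measured at T3:

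- State that the long-term claims in aims (a) and (b) rest on the T3 differences PAC minus control, StEx minus control and PAC minus StEx. Estimate each with a 95% confidence interval from a repeated-measures model with a separate arm effect at each visit, adjusted for baseline.
- Treat the group and group-by-time tests as supportive, and report the T1 contrasts separately as the short-term effect.
- Estimate the T3 contrasts from the observed data by a likelihood-based model instead of LOCF, so that month-4 values are not carried into month 16. State the missing-at-random assumption that this relies on.

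Data and visits are unchanged. The cost is wording and slightly more analysis work, and a significant omnibus test driven by month 4 can no longer be called long-term effectiveness. One choice remains open: each contrast is at 5%, and the chance that at least one of the two comparisons with control rejects under no effect was about 9% in simulation. The plan should say how that is handled.
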